## Abstract

**Background:**

Eating disorders (EDs) are a group of mental illnesses associated with significant psychological and physiological consequences. Overall, only about one-fifth of individuals with EDs receive treatment and treatment is effective for only about one-third for those who receive care. The development and implementation of effective prevention approaches for those at risk is therefore pivotal. The *Body Project* is the most effective ED prevention program for at-risk women according to several meta-analyses, but reach is limited since delivery, traditionally, has been in-person. Moreover, peer-led *Body Project* groups have been reported to produce stronger effects than clinician-led *Body Project* groups when delivered in-person. This has not yet been examined for virtually delivered *Body Project* groups. This study therefore seeks to investigate the effect of virtual *Body Project* groups delivered by peers versus clinicians on ED risk factors, ED symptoms, and prospective ED onset.

**Methods:**

Young women with body image concerns aged 16–25 years (N = 441) will be included in the study and randomized to three conditions: (i) virtually delivered *Body Project* groups led by clinicians; (ii) virtually delivered *Body Project* groups led by peers; and (iii) psychoeducational control group. Participants will complete assessments at five timepoints over two years (pretest, posttest, 6-months, 1-year, and 2-years).

**Discussion:**

Further research is needed to examine approaches to increase the potential for broad implementation of prevention of EDs. The virtual modality of the *Body Project* could markedly expand the reach for young women at risk. If findings confirm that peers can deliver virtual *Body Project* groups as effectively as clinicians, this will further enhance the implementation potential.

*Trial registration*: The present study has been registered on clinicaltrials.gov (NCT05993728).

## Background

EDs affect approximately 13% of women and 5% of males [1, 2], and are marked by chronicity and high rates of relapse, as well as substantial impairment, academic difficulties, depression, anxiety, self-harm, suicide, and morbidity [3, 4]. Risk factors for the development of EDs include female gender, adolescent age, internalization of the thin beauty ideal, body dissatisfaction, dietary restraint, and negative affect [5]. In Norway, results from a recent prevalence study in adolescents revealed that ED psychopathology was common (20%), and that the estimated prevalence of any ED was as high as 16% among adolescent girls [6]. These rates are comparable to those reported in other countries [7]. Yet, less than 20% of affected individuals receive treatment [8]. This underscores the importance of efforts to prevent the development of ED in high-risk populations. Selective ED prevention approaches specifically targets individuals at high-risk for EDs, i.e. young women > 15 years with body dissatisfaction [5].

The *Body Project*, a selective 4-hour group-based program designed specifically for young women at risk for EDs, has the strongest evidence of effectiveness in reducing ED risk factors (such as thin-ideal internalization and body dissatisfaction) and ED symptoms [9], as well as preventing future ED onset among young women [10]. The evidence base for the *Body Project* is strong and based on over 20 controlled trials including assessment-only controls [11–13] and alternative credible interventions [14, 15]. Participants who complete the *Body Project* have shown a 60% reduction in future onset of EDs relative to assessment-only control participants [14] and a 54–58% reduction in future onset of EDs relative to alternative interventions [15]. The *Body Project* was originally designed as a face-to-face intervention, limiting availability to those who could attend in person. To reduce barriers to access, Ghaderi et al. [16] examined the effectiveness of virtually delivered *Body Project* groups (1 h a week over four consecutive weeks), through Google Hangouts, among young women (N = 443) aged 15–20 years. The participants were randomized to three conditions; (i) virtually delivered *Body Project* groups; (ii) expressive writing; and (iii) wait-list control group. Groups were facilitated by psychology undergraduates. The wait-list group received the *Body Project* after the 6-month follow-up. At two-year follow-up, *Body Project* participants compared to control participants showed a 77% lower incidence of ED onset and significantly greater reductions in ED symptoms and risk factors. This suggests that virtual *Body Project* groups may be an effective prevention strategy for individuals at risk of EDs, with an increased outreach. Moreover, in-person *Body Project* groups led by peer group facilitators produced a 58% greater reduction in future onset of EDs over 4-year follow-up when implemented by peer educators versus clinicians [15], theoretically because peers are perceived as more similar to the participants and thus have greater credibility. Whether these findings extend to virtual *Body Project* groups is unclear. Peer-led groups demand fewer resources to carry out than clinician-led groups, which may facilitate broader implementation.

Finally, though the effect of the *Body Project* has a strong evidence-base, it is important to confirm that interventions affect objectively measured (as opposed to self-reported) outcomes. The *Body Project* has previously been found to affect four objective outcomes, including reductions in cardiac risk [17], brain reward region response to thin models [18], attentional bias for the thin ideal [19], and positive implicit attitudes toward the thin ideal [20]. However, no research has investigated whether the *Body Project* affects objective (implicit) outcomes when implemented virtually. More insight into such implicit and explicit mechanisms of change after *Body Project* participation may inform refinements of the script that will improve the effectiveness of the *Body Project*.

In sum, the *Body Project* has consistently demonstrated its effectiveness in reducing ED risk factors, symptoms, and future ED onset across several independent research teams and countries, including England [21], USA [15], China [22], Saudi Arabia [23], Mexico [24], and Brazil [25]. However, further steps are needed to increase reach, reduce practical barriers, and enhance the potential for broad implementation for individuals at risk. Further, the recently reported prevalence estimates of EDs in Norwegian youth [6] especially among girls, point to the need to confirm effectiveness of a brief evidence-based prevention program specifically targeting this at-risk group in Norway. Additionally, confirming whether peers can effectively deliver the *Body Project* in a virtual format [26] will be important for broad nation-wide implementation.

## Research aims and hypotheses

The overall objective of this study is to evaluate the effectiveness of the *Body Project*. Specifically, the following hypotheses will be tested:

Participants in both peer-led or clinician-led virtually delivered *Body Project* groups will show significantly greater reductions in ED risk factors and symptoms compared to controls.Participants in both peer-led or clinician-led virtually delivered *Body Project* groups will show a significantly lower rates of ED onset over the 2-year follow-up than controls.Participants in both peer-led or clinician-led virtually delivered *Body Project* groups will show significant reductions in positive implicit attitudes towards the thin ideal compared to controls.Participants in peer-led (young female students) virtually delivered *Body Project* groups will show significantly greater improvements in outcomes than participants in clinician-led virtually delivered *Body Project* groups.

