### Statistical analyses

*Model building.* Intent-to-treat (ITT) analyses of condition effects will be evaluated using mixed effects growth models fit with SAS 9.2 PROC MIXED [50]. Individual variability in outcomes from posttest to 2-year follow-up was modeled adjusting for pretest outcome values. Following Singer and Willet [51], when constructing the longitudinal models we will (a) examine empirical growth plots; (b) fit an unconditional means model; (c) fit an unconditional linear growth model; (d) fit unconditional non-linear models; and (e) compare models of longitudinal change using the Akaike Information Criterion. Condition, time (coded in months since posttest), and a condition × time interaction will be added to the unconditional model. We will estimate a growth model for each continuous outcome. We will report the results of planned contrasts from these models, contrasting each pair of conditions, reporting condition differences in the model implied least-square means derived from the time and condition × time interactions at 1- and 2-year follow-up. We will report effect sizes that are equivalent to Cohen’s *d* [52]. We will use full information maximum likelihood (ML) estimation to impute missing data because this intent-to-treat approach produces more accurate and efficient parameter estimates than alternative analytic approaches such as analyzing only participants who provide complete data, making multiple imputation the recommended procedure for handling missing data [53]. Missing data will be imputed using PROC MI using baseline levels of the outcomes, condition, and demographic factors (age, race, and parent education). Based on the recommendations [53], we will impute 50 data sets. Model parameters and standard errors were combined following Rubin [54] and implemented using PROC MIANALYZE. Cox proportional hazard models, fit with STATA [55] will test whether eating disorder onset over 2-year follow-up was significantly lower in each condition versus each other condition. Schoenfeld residuals will be examined to test the proportional hazards assumption. Hazard ratios and number needed to treat (NNT; [56]) are provided as measures of effect size. Because hazard models accommodate right censoring, we will not impute missing incidence data. Given that 88% of the effects from previous *Body Project* trials have replicated in 22 controlled trials from independent teams [15], we will use a p-value of 0.05 for all inferential tests because this usually balances risk for type I and type II errors.

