
### Power calculation

Sample size calculation was made for incidence of EDs assessed over a 2-year follow up via diagnostic interviews as the primary endpoint. Incidence rates were obtained from the previous Swedish virtual *Body Project* RCT [16]. Based on this trial we postulated a difference in incidence of EDs of 8.8% and 2% between groups, and a hazard ratio of 0.26 during 2 years of follow-up. Then, with a significance level of 5% and a power of 90% the estimated number of patients needed was 147 in each arm, the total number needed was 441.

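### The printed 90% power on ED onset describes one two-group contrast; Hypothesis 2 concerns two arms, and 147 per arm gives about 70–77% per contrast and about 56–65% for both

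*Protocol article*

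**What the plan says.** The Power calculation section names ED incidence over 2 years, by diagnostic interview, as the primary endpoint. It gives one pair of rates ("we postulated a difference in incidence of EDs of 8.8% and 2% between groups"), one effect ("a hazard ratio of 0.26 during 2 years of follow-up") and one result: "with a significance level of 5% and a power of 90% the estimated number of patients needed was 147 in each arm", 441 in total. It does not say which two groups the contrast compares.

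The section Research aims and hypotheses states Hypothesis 2 on this endpoint: "Participants in both peer-led or clinician-led virtually delivered *Body Project* groups will show a significantly lower rates of ED onset over the 2-year follow-up" than controls.

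Under Statistical analyses, the Cox models "will test whether eating disorder onset over 2-year follow-up was significantly lower in each condition versus each other condition", and "we will use a p-value of 0.05 for all inferential tests". Nothing combines the contrasts into one decision. The Publication plan describes the onset paper as virtual *Body Project* versus control, without separating the arms.

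**The concern.** One power figure for one contrast does not describe a hypothesis about two active arms. If both arms must beat control, the chance of success is lower than for either contrast alone, and the shared control arm does not remove that loss. The printed 90% also has to be right for one contrast before it can support anything about two.

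At stake is what readers may expect of the hypothesis on the sizing endpoint. If one arm is significant and the other is not, the result may be read as a failed hypothesis. It may also be misread as a difference between peers and clinicians, the more readily because Hypothesis 4 predicts one.

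**Working it through.** **Inputs.** From Power calculation: 147 per arm, three arms, 8.8% versus 2%, hazard ratio 0.26, 5% level, 90% power. Assumed here because the article does not say: two-sided test, no dropout, independent participants, the same true incidence in both active arms.

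**Step 1: the two effect inputs disagree.** Under proportional hazards, 8.8% and 2% imply a hazard ratio of ln(0.98)/ln(0.912) = 0.22, not 0.26. Conversely, 8.8% with hazard ratio 0.26 gives 1 − 0.912^0.26 = 2.4% in the active arm. Both versions are carried below.

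**Step 2: try to reproduce 147 per arm.** Schoenfeld events for 90% power: 4(1.960 + 1.282)²/(ln 0.26)² = 23.2. Each pair of participants yields 0.088 + 0.02 = 0.108 events, so 23.2/0.108 is about 214 per arm (222 if events are first rounded up to 24). Two proportions need 231 per arm. None of these gives 147. The two-group total under Schoenfeld is 429 to 444, which brackets 441. That would fit a two-group total spread over three arms, but the article does not state its method.

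**Step 3: power of one contrast at 147 per arm.** Expected events: 147 × 0.108 = 15.9. Schoenfeld: √15.876 × |ln 0.26|/2 − 1.96 = 2.684 − 1.960 = 0.724, and Φ(0.724) = 76.5%. Two proportions give 73.5%.

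**Step 4: joint power.** I simulated 200,000 trials of 3 × 147, with onset recorded at 1 and 2 years at a constant yearly risk and a log-rank test of each active arm against the shared control:

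| Two-sided 5%, log-rank | 8.8% vs 2% | 8.8% with HR 0.26 |
|---|---|---|
| One contrast | 77% | 70% |
| Both arms beat control | 65% | 56% |
| At least one does | 88% | 84% |
| Exactly one does | 23% | 28% |

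A bivariate normal calculation with 76.5% per contrast and correlation 0.5 gives 64% for both.

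**Step 5: split the gap.** From 90% to 65% is 25 points: 90 − 77 = 13 from one contrast not having 90%, and 77 − 65 = 12 from requiring both. If each contrast did have 90%, both would have 82–83% (correlation 0.2 to 0.5).

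**Step 6: sensitivity.**
- Test, at 8.8% versus 2%: in a simulation of 2-year event counts, a likelihood-ratio statistic gives 66% for both and 90% for at least one; a Wald statistic gives 51% and 80%.
- Dropout (assumed; Schoenfeld, correlation 0.5): 10% gives 72% per contrast and 58% for both; 20% gives 67% and 52%.
- One-sided 5%, log-rank: 86% per contrast, 78% for both and 94% for at least one (81%, 70% and 91% with hazard ratio 0.26).
- Both active arms pooled against control, two-sided: 79% (Schoenfeld) or 87% (two proportions).

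**The case against.** The strongest objection is that no both-must-win rule exists. A reader might infer that the trial succeeds only if both arms are significant, and that the joint requirement alone explains the drop from 90% to 65%. The article supports neither inference. Hypothesis 2 mixes *both* and *or* and stands in a list of predictions, the Cox contrasts are tested separately, and the onset paper is described without separating the arms. Requiring both accounts for only about half of the gap. This part of the objection stands, so the both-arms figure is the power under one reading.

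It is also fair that power per pairwise contrast is ordinary practice in a three-arm trial, and that joint power could be left to a fuller document. That does not rescue the printed figure, because the article does state 90%, and at its own inputs 147 per arm does not give that for a single two-sided contrast.

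A reader might also infer that a split result is the likely outcome. It is not: at 8.8% versus 2% its chance is about 23%, against 65% for both significant. The plan also has a direct peer-versus-clinician contrast and nowhere infers a difference from discordant p-values. The risk lies in interpretation and is moderate.

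Finally, 65% should not be presented as exact. The test, sidedness and effect input all move it.

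**Conclusion.** The point holds in limited form. The stated 90% is not the power for Hypothesis 2 under any of the three readings of its wording. With a two-sided log-rank test and no dropout, power is about 70–77% per contrast, about 56–65% for both arms and about 84–88% for at least one. The lower figure in each pair uses hazard ratio 0.26 and the higher uses 2%.

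Two separate faults contribute about equally: the sample size does not give 90% for one contrast, and a single-contrast figure is set beside a two-arm hypothesis. Correcting only the first would still leave both arms at about 82–83%.

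The conclusion rests on two-sided testing and equal true effects in the active arms. The per-contrast and both-arms figures stay below 90% even one-sided. The at-least-one figure does not: it reaches 90% with a two-sided likelihood-ratio test and exceeds it one-sided. Dropout lowers the per-contrast and both-arms figures.

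**What to change.** In Power calculation, replace the 90% with the power per contrast (about 70–77%) and the power for both arms (about 56–65%). State the test, its sidedness, and which of the two inconsistent inputs (2% or hazard ratio 0.26) is used.

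In Research aims and hypotheses, replace the mixed *both … or* wording in Hypothesis 2. Use either an explicit claim that each arm beats control, or two separate hypotheses (peer-led versus control; clinician-led versus control), each with its own power. Add that one significant and one non-significant contrast is not evidence that peers and clinicians differ. If the arms are equally effective, that pattern has about a 23% chance at 8.8% versus 2%; a claim of difference rests on the direct contrast.

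The cost is wording and a less favourable stated power. No extra participants are needed.

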## Methods and design

### Design

This is a randomized controlled trial (RCT) with three arms; (i) clinician-led virtual *Body Project* groups; (ii) peer-led virtual *Body Project* groups; and (iii) psychoeducational control group.

## The intervention

The *Body Project* is a group-based ED prevention program based on the principles of cognitive dissonance. According to Festinger [27], cognitive dissonance occurs when there is an inconsistency between one’s beliefs and one’s actions. This inconsistency creates psychological discomfort, which motivates the individual to reduce cognitive discord by changing their beliefs to align with their actions. In the *Body Project*, participants collectively critique the thin beauty ideal through a series of verbal, written, and behavioral exercises. Engaging in these activities prompts participants to align their attitudes with their publicly displayed behaviors, which results in a reduction in pursuit of the thin beauty ideal, which in turn is theorized to reduce body dissatisfaction and ED symptoms. Consistent with this theory, reductions in pursuit of the thin beauty ideal mediated the effects of the *Body Project* on ED symptom reduction [28]. During the four sessions, the participants define the appearance ideal, discuss costs of pursuing this ideal, attempt to dissuade group facilitators from pursuing the appearance ideal in role-plays, and engage in discussions about the negative effects of social comparison [29] and social media. Written home exercises are conducted between sessions and debriefed with the group in the following meeting. We have previously translated the latest version of the *Body Project* script [15] to Norwegian for the first time and piloted a diabetes-specific version among Norwegian young women with type 1 diabetes [30]. No further adaptations were considered necessary to obtain cultural fit, which is similar to experiences reported in the Swedish virtual *Body Project* study [16]. The *Body Project* is largely participant-driven given the Socratic open questions in line with dissonance-theory, which may explain why minimal changes are required to obtain efficacy in different countries. For example, in session 1 group facilitators ask what the society tells us that young women should ideally look like, by which the participants themselves define the appearance ideal in their own cultural context.

### Participants

A total of 441 young women will be included in the study. Inclusion criteria are being female, age between 16 and 25 years, and at least some level of self-reported body dissatisfaction verbally confirmed by the participant in the screening call, following procedures used in previous trials [14, 15, 31]. Participants diagnosed with an ED will also be included. These individuals have shown to display larger reductions in ED symptoms than participants without EDs in response to the *Body Project d* = 0.71 vs. 0.17) [32]. Exclusion criteria include being hospitalized or currently in treatment for an ED.

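### Women who already have an eating disorder count towards the 441, but they cannot have a new onset, so fewer than the stated 147 per arm are at risk for the primary endpoint

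*Protocol article*

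**What the plan says.** Under Power calculation the Protocol article states: "Sample size calculation was made for incidence of EDs assessed over a 2-year follow up via diagnostic interviews as the primary endpoint". The inputs are given as "we postulated a difference in incidence of EDs of 8.8% and 2% between groups" and "a hazard ratio of 0.26 during 2 years of follow-up", with a 5% significance level and 90% power. The rates come from the earlier Swedish virtual trial. The result is 147 per arm and 441 in total.

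Under Participants: "A total of 441 young women will be included in the study". The same paragraph adds "Participants diagnosed with an ED will also be included" and "Exclusion criteria include being hospitalized or currently in treatment for an ED". Untreated women who already meet ED criteria are therefore eligible and belong to the 441.

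Under Procedure, diagnostic interviews take place at baseline, one year and two years, and randomisation follows completion of the baseline assessment. Under Statistical analyses, Cox models "will test whether eating disorder onset over 2-year follow-up was significantly lower in each condition versus each other condition".

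**The concern.** The number said to be needed and the number to be enrolled are the same, 441, but they do not count the same women. The first is a requirement for an incidence endpoint, which only women free of an ED at baseline can reach. The second knowingly includes women who already have one. No inflation for them appears in the calculation.

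An analysis plan can define who is at risk, but it cannot restore participants who were never at risk. If baseline cases leave the onset analysis, as the words incidence and onset imply, each pairwise comparison rests on fewer women and fewer events than the stated power assumes. With about 16 events expected per comparison even at full numbers, each lost event matters.

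**Working it through.** **Inputs.** From Power calculation: two-year rates 8.8% and 2%, hazard ratio 0.26, alpha 5% (two-sided assumed, since sidedness is not stated), power 90%, 147 per arm. The baseline ED share f is not in the document and is varied from 5% to 30%. Background offers two population anchors: about 13% of women, and "the estimated prevalence of any ED was as high as 16% among adolescent girls" in Norway.

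**Step 1: the plan's own figure.** Schoenfeld events = 4 × (1.960 + 1.282)² / (ln 0.26)² = 23.2, rounded up to 24. Women per arm = 24 / (0.088 + 0.02) = 222. A two-proportion calculation gives 231 per arm. The stated 147 is not reproduced. At 147 per arm the expected events are 147 × 0.108 = 15.9, and power = Φ(√15.9 × 1.347 / 2 − 1.960) = Φ(0.72), about 77%. That shortfall exists with no baseline cases at all and is a separate point. Two starting values are therefore carried forward: 90% as stated and 77% as recomputed.

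**Step 2: number at risk.** n(f) = 147 × (1 − f). At f = 16%: 147 × 0.84 = 123.5.

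**Step 3: power on that number.**
- At face value (90% at 147 per arm), information scales with the number at risk: power = Φ(3.242 × √(1 − f) − 1.960). At 16%: Φ(3.242 × 0.917 − 1.960) = Φ(1.01), about 84%.
- By Schoenfeld with the stated inputs: events = n(f) × 0.108, power = Φ(√events × 1.347 / 2 − 1.960). At 16%: 13.3 events, Φ(0.50), about 69%.

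| Baseline ED share (assumed) | At risk per arm | Expected events per comparison | Power, 90% at face value | Power, Schoenfeld |
|---|---|---|---|---|
| 0% | 147 | 15.9 | 90% | 77% |
| 5% | 139.7 | 15.1 | 88% | 74% |
| 10% | 132.3 | 14.3 | 87% | 72% |
| 13% | 127.9 | 13.8 | 86% | 71% |
| 16% | 123.5 | 13.3 | 84% | 69% |
| 20% | 117.6 | 12.7 | 83% | 67% |
| 30% | 102.9 | 11.1 | 77% | 61% |

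The cost of admitting baseline cases is the fall within a column. At 16% this is about 6 points on the stated power and about 8 points on the recomputed power.

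**The case against.** Four points can be made for the plan.

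- **The risk set may be defined elsewhere.** This is a condensed article, and an analysis plan commonly defines the onset set. That stands: silence on an ED-free set is not in itself an error. It does not answer the count, because removing baseline cases is exactly what takes the number below 147.
- **The share is unknown.** That also stands. The anchors are population figures; selection for body dissatisfaction may raise the share and exclusion of treated cases may lower it. At 5% to 10% the loss is only 2 to 5 points. Hence a range and no single figure.
- **The source rates may already contain the loss.** If the Swedish trial divided onsets by all randomised women, part of the shortfall is built into 8.8% and 2%. The article does not say which denominator was used.
- **Including women with an ED is deliberate.** The Participants section gives a reason, a larger symptom response in that group, and the symptom hypothesis is not restricted to ED-free women. This is a fair ground for enrolling them, but not for counting them towards an incidence sample size.

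Two stronger readings are tempting. One is that women still ill at one or two years will be counted as onsets, which would dilute the hazard ratio. The article nowhere says so, and any figure for that dilution would need an invented persistence rate in each arm. The other is that the symptom results are invalid as evidence of prevention because women with an ED respond more. The hypothesis as worded covers all participants, so this is a matter of reporting and not an error.

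**Conclusion.** The point holds in a limited form. The enrolled 441 includes women who are not at risk of the primary endpoint, the calculation makes no allowance for them, and the stated 90% is therefore not delivered for the onset comparison. At a 16% baseline share power is about 84% if the stated figure is trusted and about 69% by Schoenfeld; over 5% to 30% the ranges are 88% to 77% and 74% to 61%.

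The direction follows from the document. The size rests on four assumptions: the baseline share, a two-sided test, the stated rates applying to ED-free women, and onset meaning a first positive diagnosis in a woman negative at baseline and not a new episode after remission, which the article does not define. A reader might attribute the whole distance from 90% to 69% to the baseline cases. That would be wrong, because the part from 90% to 77% comes from the sample-size calculation itself.

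**What to change.** State that the Cox onset analysis uses randomised participants who are EDA-5 negative at baseline. Status is known before randomisation, so the restriction does not disturb the comparison of arms. It also rules out counting persisting illness as onset; the EDA-5 covers the preceding three months, so a positive follow-up interview cannot by itself tell the two apart.

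Then give the expected baseline ED share and restate power on the expected ED-free number per arm, saying which denominator lies behind 8.8% and 2%. The cost is a few sentences and a less favourable stated power.

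Optional: stratify randomisation on baseline EDA-5 status, and report symptom effects by that status. Enlarging the trial to keep 147 ED-free women per arm is a different and costly decision: at a 16% share it means 147 / 0.84 = 175 per arm, or 525 in total. Correcting the plan does not require it.
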